***Background and rationale***

Each year approximately 5.1 million people undergo surgery representing a large proportion of NHS activity(1). Complications arise in one in five surgical procedures, which leads to prolonged hospital stays and higher costs associated with surgery and staying in hospital(2). The 30-day mortality rate of surgery is 1%, but one-year mortality rates increase by two-fold if a patient experiences a complication within the first 30 days after surgery(1, 2). Currently it is unknown how many times the average person will have surgery during their lifetime and thus how much surgical healthcare resources the average person will use over their lifetime.

Lifetime risk is a measure of the risk of an event occurring throughout an average person’s lifetime. It is a measurement that is used commonly to calculate a patient’s risk of developing a certain disease, for example breast cancer or cardiovascular disease, but it has not been used to assess the risk of a patient undergoing any type of surgery during their lifetime(3, 4). Knowing a patient’s lifetime risk of undergoing surgery could potentially help public health strategists anticipate and plan for the future burden of surgery, potential complications and mortality. Ideally, to calculate the lifetime risk of a patient undergoing surgery we would use a cohort study to assess a population across their lifetime and investigate if and at what age participants undergo surgery and when the participants die. However, this has limited feasibility at a population level. Instead, we will use two validated methods to calculate the lifetime risk of surgery: life tables and cumulative risk.

The COVID-19 pandemic has changed how healthcare is delivered and led to large changes in resource allocation(5). The pandemic has had a clear impact on surgery and waiting lists. However, the magnitude of this has not yet been quantified(6). This unmeasured impact could have influenced the lifetime risk of undergoing surgery during the pandemic period. We will use COVID-19 as an exposure to investigate the impact it has had on the lifetime risk of surgery.

This study aims to measure the lifetime risk of undergoing surgery and report any change in the lifetime risk during the COVID-19 pandemic.

***Primary Objective:***

1. To report the population lifetime risk of surgery.

***Secondary Objective:***

1. To report the impact of the COVID-19 pandemic on the lifetime risk of surgery.
2. **Methods**

***Data source***

The study will be conducted in England. Data regarding the number of surgeries taking place will be sourced from hospital episode statistics admitted patient care (HES-APC). This database gathers information regarding all patient hospital admissions. This includes data on clinical information regarding diagnoses and operations, patient demographic information and dates of admission and discharge(7). Data on population estimates will be sourced from life tables produced by the ONS(8).

***Study design and setting***

This is a nationwide observational cohort study that will describe the number of patients undergoing surgery in aged-specific 5-year intervals in the National Health Service (NHS) in England between 1^st^ April 2015 and 31^st^ August 2020_._ This will then be compared with data on population estimates from the ONS for each 5-year age interval to calculate lifetime risk. The impact of the COVID-19 pandemic on the lifetime risk of surgery will be assessed by comparing data from a pre-pandemic period defined as __ to the ____,_ to a pandemic period defined as __ to the ____._

***Participants and data collection***

All patients, of any age, identified as undergoing surgery using HES-APC in England between 1^st^ April 2015 and 31^st^ August 2020 will be included. Surgery will be defined using the assigned Office of Population Census and Surveys Version 4 (OPCS-4) codes for hospital procedures. Surgical procedures will be identified by using a predetermined list of OPCS-4 codes(1). The number of patients undergoing surgery will be categorised into 5-year age bands. Population estimates will be found using national life tables released from the ONS, this again will be categorised into aged-specific 5-year age bands(8).

***Derivation of variables***

Age will be defined by the age that the patient was on the date of their operative procedure. The number of patients undergoing surgery will be categorised into 5-year age epochs e.g. Age 0-4, 5-9, 10-14…. until 90+. The lifetime risk will be calculated and repeated for consecutive years that we have data available, this has been done in previous papers assessing the lifetime risk of diabetes(9, 10).

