***Statistical Analysis***

There are two validated methods to measure lifetime risk – life tables and cumulative risk. We will calculate the lifetime risk of surgery using both methods, with life table’s being the primary method.

We will report the total number of patients undergoing surgery, as defined using the OPCS-4 codes, in the time frame assessed. This data will be categorised by 5-year epochs. We will then divide the total number of patients undergoing surgery for each 5-year epoch by the total population in that 5-year epoch using population estimates from ONS data. This will give us the age-specific incidence rates of surgery per head of the population.

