**Cumulative risk**

Cumulative risk can be used to estimate the lifetime risk of having surgery. This is calculated using the following equation(11):

[figure not shown]

Where P is the cumulative risk until age
[figure not shown]
, C_x_ is the total number of surgeries in age group
[figure not shown]
 and n_x_ is the number of person-years of age group
[figure not shown]
. This is multiplied by 5 as 5-year epochs are used. This will be calculated with a 95% confidence interval.

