**Sample table 2: Incident rate**

|  | **__ to __** | | **__ to __** | |
| --- | --- | --- | --- | --- |
| **Age groups (years)** | **Number of patients undergoing surgery** | **Person-years lived** | **Number of patients undergoing surgery** | **Person-years lived** |
| **0-4** |  |  |  |  |
| **5-9** |  |  |  |  |
| **10-14** |  |  |  |  |
| **15-19** |  |  |  |  |
| **20-24** |  |  |  |  |
| **25-29** |  |  |  |  |
| **30-34** |  |  |  |  |
| **35-39** |  |  |  |  |
| **40-44** |  |  |  |  |
| **45-49** |  |  |  |  |
| **50-54** |  |  |  |  |
| **55-59** |  |  |  |  |
| **60-64** |  |  |  |  |
| **65-69** |  |  |  |  |
| **70-74** |  |  |  |  |
| **75-79** |  |  |  |  |
| **80-84** |  |  |  |  |
| **85-89** |  |  |  |  |
| **90+** |  |  |  |  |

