**Appendix 2**

### *The Life Table Method*

We calculated lifetime risk for both men and women in a sex-differentiated fashion because the life table method does not allow combined analyses. The incident rate of surgery in person-years was calculated for each 5-year epoch. We calculated surgical mortality rate and the all-cause mortality rate in person-years for each 5-year epoch.

The probability of no longer being alive and surgery free was calculated using equation 1^4^:

$$\lambda_{i}=r_{i}+m_{i}-s_{i}$$

Where $r_{i}$ is the incident rate of surgery in person years, $m_{i}$ is the all-cause mortality rate and $s_{i}$ is the surgical mortality rate. The probability of being alive and without previous surgery at age i was calculated using equation 2^4^:

$$S_{0}(i)=exp[-5\sum_{x=5}^{i} \lambda_{i}]$$

This was multiplied by 5 due to 5-year epochs being used.

Lifetime risk at age *i* was then calculated using equation 3^4^:

$${l_{i}=S}_{0}(i)\times r_{i} \times\frac{1-exp(-{5(\lambda}_{i}))}{\lambda_{i}}$$

The lifetime risk for period *y* (e.g. from 0-90) is calculated using equation 4^4^:

$$LR(y)= \sum_{i=0}^{90} l_{i}(y)$$

*Cumulative Lifetime Incidence*

Cumulative incidence was also used to estimate the lifetime risk of surgery, it was possible to calculate the overall cumulative lifetime incidence of first and all surgery as this method does not rely on mortality rates so male and female data can be combined. We calculated this using equation 6^10^:

$$P=1-exp(-5\sum_{x=5}^{i} r_{i})$$

Where P was the cumulative incidence until age i and $r_{i}$ is the incidence rate in person-years. This was multiplied by 5 as we used 5-year epochs.

**Supplementary figure 1:** Men (blue line) compared to women (red line) cumulative lifetime incidence of first surgery based on the years 2016-19. Error bars are the 95% CIs.

**Supplementary figure 2:** Men (blue line) compared to women (red line) cumulative lifetime incidence of all surgery based on the years 2016-19. Error bars are the 95% CIs.

**Supplementary figure 3:** Pre-pandemic (blue line) compared to the pandemic (red line) lifetime risk of all surgery for men and women (Error bars are 95% CIs). The pre-pandemic period was based on data from 2016-19 and the pandemic period was based on data from 2020. This was calculated using the life table method.

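### The SAP does not fix what is counted or over what window; under the Sample table 2 layout, unequal windows bias the pandemic rate ratio upward

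*SAP*

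**What the plan says.** **Numerator.** Derivation of variables states: "The number of patients undergoing surgery will be categorised into 5-year age epochs". Statistical Analysis ties the count to the whole period: "We will report the total number of patients undergoing surgery, as defined using the OPCS-4 codes, in the time frame assessed". Sample table 2 has, for each of two periods, one column headed "Number of patients undergoing surgery". Cumulative risk uses another unit; its C term "is the total number of surgeries in age group". Appendix 2 has two endpoints ("it was possible to calculate the overall cumulative lifetime incidence of first and all surgery") but does not say which count stands behind the rate r.

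**Denominator.** Statistical Analysis divides "by the total population in that 5-year epoch using population estimates from ONS data", which is a head count. Sample table 2 has "Person-years lived".

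**Windows.** Study design and setting leaves the comparison dates blank, as do the column heads of Sample table 2. The legends of Supplementary figures 3 and 4 supply them: "The pre-pandemic period was based on data from 2016-19 and the pandemic period was based on data from 2020". Participants and data collection ends the data on 31 August 2020.

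**Repeat operations.** No section says whether a patient with several operations counts once per period, per year, per age band or per operation. Derivation of variables does say that lifetime risk will be repeated for consecutive years.

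**The concern.** Person-years grow in proportion to the length of the window. The number of distinct patients does not, because second and later operations on the same person in the same band add nothing. At a constant operating rate, patients per person-year therefore falls as the window lengthens, and dividing by person-years does not correct it. Comparing four years with eight months then compares two differently deflated rates.

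The pandemic contrast is the SAP's only secondary objective. Its size, and even its apparent direction, could follow from an unstated aggregation rule rather than from any change in surgery.

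**Working it through.** The SAP states no rate, sample size or expected effect, so there is no figure of its own to reproduce.

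**Inputs**
- Windows: T = 4 years (2016-19 read as calendar years) and T = 8/12 = 0.667 year (January to August 2020).
- Age bands: 5 years, by age at operation (Derivation of variables).
- Operation rate λ = 0.09 per person-year. This is an assumption: 5.1 million a year (Background and rationale) over an assumed 56 million gives 0.091. The SAP's figure is for people, not operations, so it is only a guide.
- Clustering of repeat surgery: gamma variance θ = 0 (none), 1 and 2. This is an assumption; the documents give nothing on it.

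**Formulas**
1. Share of people with at least one operation in T years: D(T) = 1 − exp(−λT) for θ = 0, and D(T) = 1 − (1 + θλT)^(−1/θ) otherwise.
2. Without band crossing, the rate is D(T)/T.
3. With ages uniform within bands, a share T/5 of people cross a boundary during the window and can count in both bands. Expected counts are N(T) = (1 − T/5)·D(T) + (2/5)·∫₀ᵀ D(u)du, and the rate is N(T)/T.

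**Worked case, θ = 0**
- Four years: D = 1 − exp(−0.36) = 0.3023 and the integral is 4 − 0.3023/0.09 = 0.641. N = 0.2 × 0.3023 + 0.4 × 0.641 = 0.317, so the rate is 0.0792.
- Eight months: D = 1 − exp(−0.06) = 0.0582 and the integral is 0.0196. N = 0.867 × 0.0582 + 0.4 × 0.0196 = 0.0583, so the rate is 0.0875.
- Ratio: 0.0875/0.0792 = 1.10.

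**Results at λ = 0.09, once per band per period over person-years.** The last column sets λ = 0.072 in the pandemic window.

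| θ | Pre-pandemic rate | Pandemic rate, no true change | Ratio | Ratio without band crossing | True 20% fall shows as |
|---|---|---|---|---|---|
| 0 | 0.0792 | 0.0875 | 1.10 | 1.16 | −11% |
| 1 | 0.0716 | 0.0851 | 1.19 | 1.28 | −4% |
| 2 | 0.0658 | 0.0829 | 1.26 | 1.39 | +2.5% |

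All these rates lie below 0.09. The pandemic rate is high only relative to a more deflated pre-pandemic rate.

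**Range.** With band crossing, λ from 0.05 to 0.15 and θ from 0.5 to 4 give ratios of 1.08 to 1.55. If 2016-19 means three years, the ratios at λ = 0.09 are 1.08, 1.15 and 1.20 for θ = 0, 1 and 2.

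**Other readings of the SAP, λ = 0.09, no true change**
- Operations over person-years (the unit in Cumulative risk): ratio 1.00.
- Patients counted by calendar year, 12 months against 8: about 1.015 to 1.04 for θ = 0 to 2.
- Patients over a head count, D(0.667)/D(4): 0.0582/0.3023 = 0.19, 0.0566/0.2647 = 0.21 and 0.0551/0.2375 = 0.23 for θ = 0, 1 and 2. This is a large spurious fall.
- First operation since 1 April 2015, over all person-years. The rate is [D(b) − D(a)]/(b − a), with a to b running from 0.75 to 4.75 years and from 4.75 to 5.417 years after that date. The ratios are 0.0570/0.0706 = 0.81, 0.0424/0.0591 = 0.72 and 0.0340/0.0511 = 0.67. This too is a spurious fall.

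**The case against.** The strongest objection is that once-per-period counting is inferred. The patient numerator comes from the main text and Sample table 2, where the dates are blank. The windows come from legends in Appendix 2. The December 2023 change log defines r only as an incident rate in person-years. Derivation of variables repeats the calculation for consecutive years, which would remove most of the bias. In Appendix 2, counting operations for all surgery gives no bias, and counting a person once is what a first-surgery risk requires.

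Much of this stands. It limits the point to a conditional one and takes away certainty about direction. It does not remove the point. Impact of COVID-19 Pandemic generates the age epochs for each period, and Sample table 2 has one pair of columns per period, so yearly counting is not specified for the contrast. Nor does any section settle the unit.

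A reader might infer that the plan inflates the pandemic rate and hides a real fall. The documents do not support that as a general statement: it holds for patients over person-years, while a head count or unequal look-back pushes the other way. A reader might also take the 28% to 39% excess from D(T)/T as the size of the bias. That formula keeps everyone in one band for the whole window, although with 5-year bands 4/5 = 80% of people cross a boundary within four years.

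**Conclusion.** The point holds in conditional form. The counting unit and denominator are inconsistent across sections, and the implied windows are very unequal. Under the layout of Sample table 2 the rate ratio is biased upward by about 10% without clustering and 19% to 26% with gamma variance 1 to 2, at 0.09 operations per person-year. A true 20% fall would usually be attenuated; it would vanish only with moderate clustering.

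These figures rest on the assumed rate and clustering, uniform ages within bands, and calendar-year windows. They apply to rates; their effect on lifetime risk also depends on age-specific rates and mortality that the SAP does not give. The need for one counting rule does not depend on the assumptions, because the permitted readings disagree in direction.

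**What to change.** - Use person-years as the denominator throughout.
- Use equal-length, calendar-matched windows: for example, the same months of each pre-pandemic year as are available in 2020, averaged over those years.
- For the all-surgery series, count operations, as Cumulative risk does.
- For the first-surgery series, count first operations with the same look-back length in both periods, and state that length.
- Put the dates into Study design and setting, and relabel Sample table 2 with the event, window and denominator for each series.

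With equal windows, or with operations counted over person-years, the ratio under no true change is 1.00. The change affects the aggregation step and table headers and needs no new data.

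The cost is some precision. Only part of each pre-pandemic year enters the contrast, and equal look-back shortens the usable data. With data from 1 April 2015, a window starting in January 2016 has nine months of look-back; requiring more would drop that year. The text should also say that a first operation means the first within the stated look-back, not the first ever.

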***Outcomes***

*Primary outcome*

1. A surgical procedure defined according to a standard definition.

*Secondary outcome*

1. Death among patients who have had surgery.
2. **Statistical analysis**

***Statistical Analysis***

There are two validated methods to measure lifetime risk – life tables and cumulative risk. We will calculate the lifetime risk of surgery using both methods, with life table’s being the primary method.

We will report the total number of patients undergoing surgery, as defined using the OPCS-4 codes, in the time frame assessed. This data will be categorised by 5-year epochs. We will then divide the total number of patients undergoing surgery for each 5-year epoch by the total population in that 5-year epoch using population estimates from ONS data. This will give us the age-specific incidence rates of surgery per head of the population.

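### The main text divides patients by population per head, whereas the formulas and the incident-rate table shell need a rate per person-year; the two rules must be reconciled

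*SAP*

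**What the plan says.** The Statistical Analysis section sets out the rate in three steps.

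- Numerator: "We will report the total number of patients undergoing surgery, as defined using the OPCS-4 codes, in the time frame assessed".
- Division: "We will then divide the total number of patients undergoing surgery for each 5-year epoch by the total population in that 5-year epoch", with the population taken from ONS estimates.
- Label: "This will give us the age-specific incidence rates of surgery per head of the population".

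Elsewhere the denominator is person-time.

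- Cumulative risk section: the denominator n_x "is the number of person-years of age group", and the sum is multiplied by 5.
- Sample table 2 (Incident rate): each of the two compared periods has its own column headed "Person-years lived".
- Change log and Appendix 2, life table method: "The incident rate of surgery in person-years was calculated for each 5-year epoch". The rate r_i then enters equations 1 to 4 with a factor of 5.
- Appendix 2, cumulative lifetime incidence: r_i is again a person-years rate, multiplied by 5.

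Sample table 1, the shell for the life table, shows a Population column beside the incident rate. The data window is 1 April 2015 to 31 August 2020. The period dates are not filled in under Study design and setting, but the Appendix 2 figure captions give them: "The pre-pandemic period was based on data from 2016-19 and the pandemic period was based on data from 2020".

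**The concern.** A count accumulated over a window and divided by a head count is a proportion for that window. Its size depends on how long the window is. The formulas multiply by the 5-year width of the age band, so the quantity they take must be per year. A per-head figure has the right units only when the window happens to be one year.

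This matters because r_i feeds the primary objective (lifetime risk by both methods) and the secondary objective (pre-pandemic against pandemic). The two compared periods differ greatly in length, so a rule that does not remove window length would put that difference into the contrast. The change log says that it amends the life table method. It does not withdraw or reword the general rule in the Statistical Analysis section, which is also the only place that names both the division and the ONS source of its denominator.

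**Working it through.** The SAP states no numeric rate, event count or sample size, so there is no figure of its own to reproduce. The check compares the two rules.

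**Inputs from the SAP**
- Full window: 1 April 2015 to 31 August 2020 = 65 months = 65/12 = 5.42 years.
- Pre-pandemic period: 2016-19, read as four calendar years.
- Pandemic period: 2020. If cut at the end of the data window, January to August = 8/12 = 0.667 year. A full year is shown as the alternative.
- Formula: P = 1 − exp(−5 Σ r), here over 18 five-year bands (ages 0 to 89), so 5 × 18 = 90 years.

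**Step 1: scaling of the rate.** Let the true annual rate be r and the window T years. Person-years give rT/T = r. The per-head rule gives rT.
- Full window: inflated 65/12 = 5.42-fold.
- 2016-19: inflated 4-fold.
- January to August 2020: multiplied by 0.667.
- Contrast with operating unchanged: 4/0.667 = 6.0-fold, or 4/1 = 4-fold if 2020 is a full year. With person-years the ratio is 1.00.

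**Step 2: each patient counted once per window.** The main text counts patients, so scaling may be less than linear. With the count per head as 1 − exp(−rT), the ratio of 2016-19 to 2020 is as follows.
- Eight months of 2020: (1 − e^(−4r))/(1 − e^(−0.667r)) = 5.9 at r = 0.01 and 5.2 at r = 0.09.
- Full-year 2020: (1 − e^(−4r))/(1 − e^(−r)) = 0.0392/0.00995 = 3.9 at r = 0.01 and 0.302/0.0861 = 3.5 at r = 0.09.

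**Step 3: what this would do to lifetime risk (illustration only).** Assume a constant r = 0.01 per year. For the life table, also assume all-cause mortality m = 0.01 per year and surgical mortality s = 0, with survival taken to the start of each band. Constant rates reduce equations 1 to 4 to R/(R + m) × [1 − exp(−90(R + m))], where R is the rate entered.

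| Rate entered | R | Cumulative risk to 90, 1 − exp(−90R) | Life table to 90 |
|---|---|---|---|
| Person-years | 0.01 | 59.3% | 41.7% |
| Per head, four-year count | 0.04 | 97.3% | 79.1% |
| Per head, eight-month count | 0.00667 | 45.1% | 31.1% |

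The second and third rows describe the same unchanged operating rate. The gap between them is window length alone. These percentages move with the assumed rates; the factors in Step 1 do not.

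**The case against.** The strongest reply is that no formula with a legible rate input takes it from the per-head sentence. The Cumulative risk section and both methods in Appendix 2 define the rate in person-years. The amended life table text, which governs the primary method, restates the rate itself in that unit. Sample table 2 gives person-years separately for each period, which is exactly the normalisation that the main-text sentence omits. All of this stands. An analyst who follows those places gets a ratio of 1.00 when operating is unchanged.

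Two further points have weight. The phrase about the time frame sits in the sentence on what will be reported, not in the division itself. The Derivation of variables section has lifetime risk repeated for consecutive years, and for a full one-year count, patients over population is close to a rate per person-year. That reading is possible for the yearly series. It does not cover a four-year pooled period, a part-year 2020 or the full 65-month window.

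The 6-fold figure also depends on reading 2016-19 and 2020 as calendar years and joining them to the 31 August cut-off, hence the range of 4 to 6.

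A reader might infer that the pandemic contrast is an artefact, or that the lifetime risk will be driven towards 100%. The SAP does not support either inference. Both would require putting a per-head count into equations whose own definitions call for person-years.

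**Conclusion.** The rule in the Statistical Analysis section is wrong as written for any window other than one year, and it contradicts the Cumulative risk section, Sample table 2, the change log and Appendix 2. Followed literally, it would inflate the rate up to about 5.4-fold over the full window. It would also create a spurious contrast of about 4- to 6-fold between 2016-19 and 2020, or about 3.5- to 5.9-fold if each patient is counted once per window and annual rates lie between 0.01 and 0.09. The linear factors rest on the SAP's dates and the calendar-year reading. The lifetime-risk percentages rest on assumed rates and show direction only.

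This is a conflict between two stated rules for a key input, not evidence that the planned contrast is invalid. It is worth correcting because the input serves both objectives. In addition, the passages that name person-years do not say how to form them from ONS estimates when a period covers part of a year.

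**What to change.** Replace the division in the Statistical Analysis section with a definition along these lines: for each age band and period, r_i is the number of events in the band during the period (first or all surgery, whichever the analysis counts) divided by the person-years in that band during the same period. Person-years are the ONS population of England in the band times the period's actual length in years, summed over calendar years.

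- State the part-year rule. Data for 2020 to 31 August carry 8/12 of a year, and April to December 2015 carries 9/12 if the yearly series uses calendar years. If it uses April-to-March years, there are five full years and a remainder of 5/12. Say which applies.
- Delete the per-head label.
- Align the Population column of Sample table 1 with the person-years columns of Sample table 2.

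The cost is a sentence or two of SAP wording and one column heading. No new data are needed, and the lifetime-risk formulas need no change for this point.

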**SAP: Sample tables and flow chart**

**Sample table 1: Life Tables**

| **Age (years)** | Population | Incident rate of surgery | Mortality rate for those undergone surgery | Mortality rate for those who have not undergone surgery | Probability of transition from no surgery to surgery | Probability of transition from no surgery to death | Probability of transition from surgery to death | Proportion of hypothetical cohort undergoing surgery |
| --- | --- | --- | --- | --- | --- | --- | --- | --- |
| **0-4** |  |  |  |  |  |  |  |  |
| **5-9** |  |  |  |  |  |  |  |  |
| **10-14** |  |  |  |  |  |  |  |  |
| **15-19** |  |  |  |  |  |  |  |  |
| **20-24** |  |  |  |  |  |  |  |  |
| **25-29** |  |  |  |  |  |  |  |  |
| **30-34** |  |  |  |  |  |  |  |  |
| **35-39** |  |  |  |  |  |  |  |  |
| **40-44** |  |  |  |  |  |  |  |  |
| **45-49** |  |  |  |  |  |  |  |  |
| **50-54** |  |  |  |  |  |  |  |  |
| **55-59** |  |  |  |  |  |  |  |  |
| **60-64** |  |  |  |  |  |  |  |  |
| **65-69** |  |  |  |  |  |  |  |  |
| **70-74** |  |  |  |  |  |  |  |  |
| **75-79** |  |  |  |  |  |  |  |  |
| **80-84** |  |  |  |  |  |  |  |  |
| **85-89** |  |  |  |  |  |  |  |  |
| **90+** |  |  |  |  |  |  |  |  |

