**Supplementary figure 4:** Pre-pandemic (blue line) compared to the pandemic (red line) lifetime risk of first surgery for men and women (Error bars are 95% CIs). The pre-pandemic period was based on data from 2016-19 and the pandemic period was based on data from 2020. This was calculated using the life table method.

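### The first-surgery equations need rates among people not yet operated on, but the only denominator the SAP states is the whole population; the size and direction of the error depend on what first means, which is not defined

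*SAP*

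**What the plan says.** The Statistical Analysis section says the analysts will "divide the total number of patients undergoing surgery for each 5-year epoch by the total population in that 5-year epoch", and adds: "This will give us the age-specific incidence rates of surgery per head of the population". In the Cumulative risk section, the denominator n_x "is the number of person-years of age group". Both are whole-population denominators.

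Appendix 2 gives the current life-table method: "The incident rate of surgery in person-years was calculated for each 5-year epoch". It does not say whose person-years these are. The rate r_i enters equation 1, λ_i = r_i + m_i − s_i, where m_i is all-cause mortality and s_i "is the surgical mortality rate", with no further definition. Equation 2 turns λ into S0(i), the probability of being alive with no earlier surgery. Equations 3 and 4 use S0 to accumulate lifetime risk. Equation 6 gives cumulative incidence as P = 1 − exp(−5Σr).

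Appendix 2 applies equation 6 to both first and all surgery. The caption of Supplementary figure 4 applies the life table to the "lifetime risk of first surgery for men and women". Neither place defines first or gives it a separate denominator. The data run from 1 April 2015 to 31 August 2020. The equations in Appendix 2 contain no term for the prevalence of past surgery.

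**The concern.** S0 describes people who are alive and have never been operated on. λ must therefore be the rate at which such people leave that state, and r must be first surgeries per surgery-free person-year. If first surgeries are divided by everyone, the rate has already been diluted by those operated on before. Putting that diluted rate through exp(−5Σr) discounts for them a second time.

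A related question concerns s_i. The subtraction m_i − s_i makes sense if s_i is deaths due to surgery over the same person-years as m_i. A rate per surgical patient has a different denominator, and λ could then fall below r or even below zero.

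Lifetime risk is the primary objective and the life table is the primary method, so these inputs determine the main result.

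**Working it through.** The SAP states no lifetime-risk value or event count, so there is no figure of its own to reproduce. The check is algebra plus a two-state model (surgery-free, operated on) in 19 five-year bands.

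**Inputs from the SAP:** equations 1-4 and 6, the whole-population denominator, the April 2015 start of data, and the 2016-19 pre-pandemic period in the figure captions.

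**Assumed inputs, not in the SAP:** a constant first-surgery hazard h; mortality either zero or 3e-5·exp(0.095·age) per year; equal mortality before and after surgery unless stated; s_i = 0 unless stated; equation 2 summed over the earlier bands.

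**1. Ceiling with lifetime-first counts.** Let π(a) be the surgery-free share of those alive at age a. With stable rates and equal mortality, first surgeries per whole-population person-year equal hπ(a), which is the rate at which π falls. Summed over life, 5Σr = 1 − π(end) ≤ 1. Equation 6 therefore gives at most 1 − exp(−1) = 63.2%. Equations 1-4 have the same limit when s_i ≤ m_i.

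Hand check with no deaths, h = 0.01 over 95 years: the true risk is 1 − exp(−0.95) = 61.3%, so 5Σr = 0.613 and equation 6 gives 1 − exp(−0.613) = 45.8%.

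**2. With mortality, lifetime-first counts.**

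| h per year | True risk | Equations 1-4, whole population | Equations 1-4, surgery-free person-years |
|---|---|---|---|
| 0.01 | 54.0% | 41.6% | 54.0% |
| 0.02 | 78.4% | 54.2% | 78.4% |
| 0.04 | 94.9% | 61.2% | 94.8% |

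**3. How firm the ceiling is.** Doubling mortality after surgery lifts 5Σr to 1.04 and equation 6 to 64.7%. Reading equation 2 as printed (sum from x = 5 through i) gives up to 71.3% in the model.

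**4. First-in-window counts.** Assume 0.75 years of look-back (April 2015 to January 2016), a four-year window, and a hazard unaffected by earlier surgery. The mean share not yet counted at h = 0.02 is exp(−0.015) × (1 − exp(−0.08))/0.08 = 0.947. With no deaths, 5Σr = 0.02 × 0.947 × 95 = 1.80. Equation 6 gives 1 − exp(−1.80) = 83.5% against a true 1 − exp(−1.90) = 85.0%. There is no ceiling at 63%.

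With mortality, equations 1-4 give 53.0%, 76.6% and 93.1% for true values of 54.0%, 78.4% and 94.9%, a shortfall of 1.0 to 1.8 points. Taking those already counted in the window out of the denominator restores h and hence the true value.

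**5. An alternative repair.** One could keep the whole-population denominator and drop r from the survival term: LR = Σ r_x·A_x·(1 − exp(−5m_x))/m_x, where A_x is survival from all-cause mortality. With lifetime-first counts this recovers the true value. With window-first counts it gives 76% for a true 54.0% and 149% for a true 78.4%.

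**6. The s_i term.** As illustration only, set s_i to 1% a year per surgical patient. Then m_i − s_i is negative in 12 of 19 bands. Even with correct surgery-free rates, 54.0% becomes 78.5% and 78.4% becomes 107.9%.

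**The case against.** A reader might infer that the first-surgery estimate is always biased down and can never exceed 63%. The SAP does not support that. The ceiling needs lifetime-first numerators, and a 2015-2020 extract does not supply these by itself. The SAP names no other source of surgical history. If first means first in the data, step 4 shows a small denominator effect, and repeat surgery counted as first works in the other direction. That objection stands, and it makes both the ceiling and the downward bias conditional. The near-agreement in step 4 is not reassurance, however: it rests on a hazard that earlier surgery does not change.

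It is also fair that the sentence on dividing by the total population concerns all patients undergoing surgery. Its use for first surgery is an inference from the absence of any other rule. For the all-surgery estimate there is no 63% limit; whole-population rates are adequate there if people with and without past surgery have the same rate.

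On s_i, a reader might conclude that it is a rate among surgical patients, since the secondary outcome is "Death among patients who have had surgery" and Sample table 1 has a column headed "Mortality rate for those undergone surgery". Neither defines s_i, and that column belongs to the transition-probability method replaced in December 2023. Appendix 2 puts surgical and all-cause mortality side by side on a person-years basis, which fits a shared denominator at least as well. The term is undefined, not shown to be wrong. The 1% a year in step 6 is an assumption; the 1% in the SAP's background is a 30-day figure and cannot be read as an annual rate.

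**Conclusion.** The mismatch is real: S0 requires rates among surgery-free people, the only stated denominators are whole-population ones, and nothing in equations 1-4 corrects for past surgery.

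- **First means first in a lifetime.** The estimate is too low, by about 12 points at a true 54.0% and 24 points at a true 78.4% under the assumed rates, with a limit of about 63%. This rests on stable rates, equal mortality after surgery, s_i ≤ m_i, and equation 2 indexed over the earlier bands.
- **First means first in the data.** There is no such limit. The denominator costs about 1-2 points under a constant hazard, misclassified repeat surgery pushes the estimate up, and the net error cannot be known from the SAP.

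Since the SAP does not say which meaning applies, the first-surgery figures cannot be interpreted until it does. The definition of s_i needs the same clarification.

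**What to change.** 1. Define first surgery and state its look-back.
2. For first surgery, match the denominator to the numerator: remove from the ONS person-years those already counted as having had surgery under that same definition. With a constant hazard this recovered the true risk under both meanings of first. A lifetime definition would need surgical history from before April 2015, for which the SAP names no source.
3. Use the formula in step 5, which drops r from the survival term, only with true lifetime-first counts. It also assumes similar mortality with and without past surgery and roughly stable rates.
4. State that s_i is deaths due to surgery over the same whole-population person-years as m_i, or omit it. Check m_i − s_i ≥ 0 in every band.

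The cost is a definition, an adjusted denominator and a little more analysis work. Misclassification from the short look-back remains and should be reported as a limitation.
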